### Statistical analysis and data management

The overall recruitment and attrition rates of the brothels and participants for the intervention arm will be described. The Intra Cluster Correlation (ICC) and the effect size will be generated in addition to the attrition rates to enable sample size estimation required for a phase III trial.

As the FSWs are nested in brothels, we will use a multilevel regression approach with three levels to assess the potential effects and viability of the intervention on condom use behavior. The first level consists of the repeated measures within the participants (baseline and follow-up measurements), the second level are the FSWs, and the third level are the brothels, where the FSWs are nested. Multilevel logistic regression will be used to analyze the effects on condom use separately for steady partners and clients. The multilevel regression analysis was chosen because this allows for data missing at random, which is less strict than the requirement of data missing completely at random [18]. Each interviewed participant will be given a code, and the questionnaires and data sets will be stored in a password-protected computer and only researchers will have access to the data.

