We conducted two different studies as formative research for the development of an intervention aimed at increasing condom use among FSWs [12]. A review of literature which showed the limited incorporation and measurement of the effect of using brothel leadership in condom promotion interventions ([name] et al., submitted-a) and an analysis of secondary data from the Integrated Biological and Behavioral Surveillance Survey ([name] et al., submitted-b) revealing the vulnerability of the young sub-population of both brothel-based female sex workers (BB FSWs) and non-brothel-based FSWs with the BB FSWs showed comparatively higher vulnerability, HIV prevalence, and risk profile.

This study aims to use a cluster randomized pilot trial approach to gain more insight into the potential of an intervention using brothel leadership to improve consistent condom use by FSWs residing in brothels. The objectives of this pilot study are to gain insight into:The feasibility of implementing the intervention within brothelsThe attrition rate for FSWs residing within the brothelsThe potential effect of the intervention on consistent condom use for FSWs within the brothel with all partner types in order to inform a sample size estimation for an adequately powered phase III trial

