### Sample size

Based on recent experience in local brothels, we anticipate that there will be between 5 and 50 FSWs in each brothel. Since this is a pilot study with the aim of providing information on the feasibility, attrition rates, and sample size estimates for a larger pilot trial, we aim to recruit 12 brothels. The formula provided by Viechtbauer et al. [17] for the calculation of sample size required for a pilot was applied in the determination of the sample size using a confidence interval of 95% and a 5% probability of existence of a problem. This resulted in a required sample size of 59 to enable the detection of feasibility problems. Due to the high attrition rate often reported in studies with FSWs and the lack of previous knowledge regarding clustering in brothels, it is unlikely that we will have all the recruited participants at follow-up; thus, we aim to recruit 200 participants to account for both aspects.

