## Discussion

This paper presents the protocol that describes a pilot study to assess the feasibility and potential effect of an intervention aimed at increasing consistent condom use and improving condom negotiation skills of BB FSWs in Abuja, Nigeria. Should the current study demonstrate feasibility, outcomes will be used to design and inform a phase III pilot cluster randomized control trial (CRCT). The aim of the phase III pilot will be to further test the effectiveness of the behavioral intervention in improving consistent use of condoms by BB FSWs in Nigeria.

The mobility of sex workers is one of the challenges faced when programming for this target group [16]. To minimize this, the intervention is designed such that the core messages and activities are delivered within a short time span, thereby enabling most of the FSWs to benefit from it before they may need to change their location.

Formative research was conducted in collaboration with the target group and the brothel leaderships for the development of the interventions; this identified important issues for the development and relevance of the intervention. Involving the brothel leaderships in the development process initially led to some resistance due to their perceived notion that the FSWs will become distracted and that they will lose the girls within their brothels. Assurance of the benefits of the intervention on the health of the FSWs and the reputation of the brothel establishment as a whole was provided. The brothel leaders were enthusiastic about the intervention and provided the needed support, without which, it will be impossible to implement the intervention.

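### The pilot's observed effect on condom use is to feed the phase III sample size, although 12 brothels cannot estimate it precisely enough for that use

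*Protocol article*

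**What the plan says.** Statistical analysis and data management names three inputs to the phase III calculation: "The Intra Cluster Correlation (ICC) and the effect size will be generated in addition to the attrition rates to enable sample size estimation". The last objective in the Background ties the effect on consistent condom use to the same purpose: "in order to inform a sample size estimation for an adequately powered phase III trial". The Discussion says that, if feasibility is shown, "outcomes will be used to design and inform a phase III pilot cluster randomized control trial (CRCT").

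The Sample size section derives 59 participants from the probability of detecting a feasibility problem. It then states "we aim to recruit 12 brothels" and, for attrition and clustering, "thus, we aim to recruit 200 participants to account for both aspects". It expects very unequal clusters ("we anticipate that there will be between 5 and 50 FSWs in each brothel") and acknowledges "the lack of previous knowledge regarding clustering in brothels". No target or minimum important difference is named anywhere in the article.

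**The concern.** This is more than detail left to a fuller document. The article states where the phase III effect size will come from, and that source is weak. A sample of 59, raised to 200, is reasonable for finding feasibility problems, but it says nothing about how well a difference between six brothels and six brothels can be estimated. If the 95% interval for the effect is wider than any plausible effect, chance largely decides the number put into the phase III formula. An estimate that is too high gives a trial that is too small; one that is too low gives a trial larger than needed; a zero or negative one gives no usable superiority sample size.

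Informing phase III is a main purpose of this pilot, so the weakness touches its principal product.

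**Working it through.** **The plan's own figure.** n = ln(1 − 0.95)/ln(1 − 0.05) = 58.4, rounded up to 59. The stated figure reproduces. It concerns seeing a problem of 5% probability at least once, and no effect or ICC enters it.

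**Inputs.** From the Sample size section: 12 brothels and 200 women. Assumed, because the article gives no figures:
- equal allocation, so 6 brothels and 100 women per arm;
- consistent use of 60%, with that variance (0.6 × 0.4 = 0.24) in both arms;
- a true difference d of 15 points;
- attrition of 0% or 30% (the article only calls it high), so n = 100 or 70 per arm, and m = 16.7 or 11.7 women per brothel;
- an ICC of 0.01, 0.05 or 0.10;
- phase III at two-sided 5% and 80% power, with its own design effect correctly known, so that only the effect estimate is in play.

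**Step 1, precision of the pilot effect.** DE = 1 + (m − 1) × ICC; SE = √(2 × 0.24 × DE/n); half-width = 2.228 × SE (t, 12 − 2 = 10 df).
- Best case (no attrition, ICC 0.01): DE = 1.157, SE = √(0.48 × 1.157/100) = 0.0745, half-width 0.166, about 17 points.
- Worst case (30% attrition, ICC 0.10): DE = 2.07, SE = √(0.48 × 2.07/70) = 0.119, half-width 0.265, about 27 points.

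Even the best case is wider than the assumed 15-point effect.

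**Step 2, phase III power if sized on the pilot estimate e.** True power = Φ(2.80 × d/e − 1.96).
- Pilot shows 20 points: 2.80 × 0.15/0.20 − 1.96 = 0.14, power 56%.
- Pilot shows 25 points: 2.80 × 0.15/0.25 − 1.96 = −0.28, power 39%.
- Power falls below 50% once e exceeds 2.80 × 0.15/1.96 = 0.214.

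**Step 3, over the distribution of e.** Take e as normal around 0.15 with the SE above, keeping positive values. Power is below 80% whenever e > 0.15, so that chance is 0.5/P(e > 0). The chance of power below 50% is P(e > 0.214)/P(e > 0). The mean comes from simulation.

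| Attrition | ICC | SE | P(e ≤ 0) | Mean power | P(power < 50%) | P(power < 80%) |
|---|---|---|---|---|---|---|
| 0% | 0.01 | 0.075 | 2% | 75% | 20% | 51% |
| 0% | 0.05 | 0.093 | 5% | 72% | 26% | 53% |
| 0% | 0.10 | 0.111 | 9% | 69% | 31% | 55% |
| 30% | 0.01 | 0.087 | 4% | 73% | 24% | 52% |
| 30% | 0.05 | 0.103 | 7% | 71% | 29% | 54% |
| 30% | 0.10 | 0.119 | 10% | 68% | 33% | 56% |

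A wider set of assumptions (50% against 60%, 65% or 70%, and 60% against 75%) gives mean power of 60–77%, below the nominal 80% throughout.

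**Step 4, precision of the ICC.** With 30% attrition there are 10 and 140 − 12 = 128 df. An estimated ICC of 0.10 gives F = (1 + 10.7 × 0.10)/(1 − 0.10) = 2.30 and a 95% interval of about 0.006 to 0.35. At 16.7 women per brothel that is a design effect from 1 + 15.7 × 0.006 = 1.1 to 1 + 15.7 × 0.35 = 6.5.

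**The case against.** Four points weigh on the other side.

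1. *Progression.* A reader might infer that phase III goes ahead only after a favourable estimate, which would select over-estimates and drop a worthwhile intervention by chance. The documents do not support this. The Discussion makes progression depend on feasibility, and the primary outcomes are brothel consent, attrition and adherence. The calculation discards non-positive estimates only because they give no usable superiority sample size. Without a further filter, over- and under-estimates are about equally likely. A claim that phase III would probably be under-powered therefore goes too far: the chance of missing 80% is little better than even. What stands is that power is unpredictable and on average below nominal.

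2. *The ICC.* A reader might infer that it will be used as a bare point value. The text says only that it will be generated; an interval may well be specified in the full protocol, and estimating an ICC is an ordinary aim of a pilot. Its imprecision is a reason for care in choosing a planning value and is not an error in the plan.

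3. *Strength of wording.* The article speaks of enabling and informing the sample size, which does not exclude considering a worthwhile difference as well. Still, the effect size is named as an input and no alternative target appears.

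4. *Pessimism of the figures.* The standard error uses follow-up data only, whereas the planned model includes baseline. If baseline removed variance as a correlation of 0.5–0.7 would (an assumption), the 23–27 points found at 30% attrition and ICC 0.05–0.10 would shrink to about 16–23, and mean power would rise to about 71–75%. Conversely, brothels of 5 to 50 women would worsen precision. The direction of the conclusion survives both.

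**Conclusion.** The point holds in a limited form. The article names the pilot's observed effect as an input to sizing phase III, and a pilot of 12 brothels cannot supply it with useful precision. On the stated assumptions, sizing on it would cost 5 to 12 points of mean power against a nominal 80%, with a one-in-five to one-in-three chance of power below 50%. Every rate, the ICC, attrition, equal allocation and the phase III error rates are assumed, so the figures illustrate the size of the problem and do not predict it. The pilot's randomisation, data collection and feasibility outcomes are unaffected, and the harm arises only if a later protocol uses the estimate as its target. This should be corrected as a cheap improvement; it is not a fatal fault.

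**What to change.** Amend the last objective in the Background and the first paragraph of Statistical analysis and data management as follows:
- Phase III will be sized on a minimum important difference in consistent condom use, agreed in advance.
- The pilot effect will be reported descriptively with a cluster-adjusted confidence interval, and will not be used as the target difference.
- The pilot will supply attrition, the control-arm proportion, the variation in brothel size, and the ICC with its interval. The planning value of the ICC will allow for that uncertainty.

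This needs no new data and no change of design, and can be done at any time before phase III is sized. The downside is that phase III may look larger on paper. For example, with an assumed control proportion of 50%, two-sided 5% and 80% power, and before clustering and attrition, a pre-agreed 15 points needs 170 women per arm, against 93 if the pilot happened to show 20 points.

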**Methods/design:**

The clusters in the randomized pilot trial will be brothels and female sex workers (FSWs) residing in the brothels will be the participants of the study. The participants will receive free condom distribution as well as HIV prevention messages on condom use and negotiation skills to increase self-efficacy in handling social and gender power plays within their environment. Twelve brothels will be randomized into experimental and control conditions with a minimum total sample size of 200 participants. Recruitment of participants will be carried out from within the brothels. The control condition will receive a standard intervention consisting of a minimum of six interactive sessions with peer educators (PE) engaging their peers through group discussions and one on one interaction using pre-designed HIV prevention messages. The experimental condition will receive the standard intervention as well as interactive sessions with the brothel leadership (chairladies and brothel managers) to facilitate consistent condom use and appropriate condom use policies, conditions, and messaging. Both interventions will be delivered over a maximum period of 16 weeks, and male and female condoms will be distributed during the intervention. Quantitative assessments will be carried out at baseline and at 16 weeks follow-up, and the pilot findings will inform feasibility of and sample size estimation for a phase III trial. The primary outcomes measured are recruitment rate attrition rate and adherence to the intervention. Consistent condom use outcomes by FSWs within the brothel with all partner types and enhanced self-efficacy for condom negotiation with all partner types will be the primary outcomes for the main study, and the feasibility of their measurement will be determined in this pilot trial.

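### As listed, the three-level condom-use model has no brothel-by-time component and no small-sample method for 12 brothels, so intervals for the intervention effect may be too narrow if brothels change differently

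*Protocol article*

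**What the plan says.** The section on statistical analysis and data management describes a multilevel regression with three levels. It says "The first level consists of the repeated measures within the participants (baseline and follow-up measurements), the second level are the FSWs", and it places brothels at the third level. It continues: "Multilevel logistic regression will be used to analyze the effects on condom use separately for steady partners and clients". An ICC and an effect size are to be produced for the phase III sample size.

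The allocation section makes the brothel the unit of randomization, after baseline data collection. On numbers, the abstract says "Twelve brothels will be randomized into experimental and control conditions with a minimum total sample size of 200 participants". The sample size section says "we anticipate that there will be between 5 and 50 FSWs in each brothel" and admits that nothing was known beforehand about clustering in brothels.

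The article does not write out the form of the intervention effect. It names no random time effect for brothels and no method for a small number of clusters.

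**The concern.** In a parallel cluster trial with a baseline and one follow-up, the uncertainty of the effect has two sources: variation between women in change, and variation between brothels in change. A brothel random intercept describes stable differences between brothels. Those differences are the same at both times, so they drop out of the baseline-to-follow-up contrast (exactly in a balanced linear model, largely in a logistic model with attrition). Without a brothel-by-time component, the contrast is assessed almost as if women had been randomized individually.

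Differential change is plausible here. Under the brothel leadership intervention, leaders give the messages, see that the sessions take place and help set condom rules in their own brothel. The discussion section reports some initial resistance among leaders. No brothel-by-time variance would mean that, apart from sampling error, all brothels in an arm shift by the same amount.

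At stake are the interval around the potential effect and the ICC passed to phase III. Both serve a stated objective of the pilot.

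**Working it through.** **The plan's own figure.** The sample size section works "using a confidence interval of 95% and a 5% probability of existence of a problem". n = ln(1 − 0.95)/ln(1 − 0.05) = 58.40, rounded up to 59. This reproduces the plan's number and is not affected by what follows.

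**Inputs from the article.** 12 brothels and 200 women, so 200/12 = 16.7 per brothel.

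**Assumptions (no figure in the article).** Six brothels per arm; 30% loss, so 140/12 = 11.7 completers per brothel (m); within-woman correlation 0.5; a range of ICCs and of brothel autocorrelation (CAC, the correlation of a brothel's effect between the two times).

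**Closed form, linear approximation, equal brothels.** Let a = 2·ICC·(1 − CAC) be the brothel part of change and b = 2·(1 − ICC)·(1 − 0.5) the woman part.

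- True variance of a brothel's mean change: a + b/m
- Variance under brothel intercepts only: (a + b)/m
- Actual error of a nominal 5% test: 2·[1 − Φ(1.96 × model SE/true SE)]

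Worked case, ICC 0.10 and CAC 0.5: a = 0.10, b = 0.90. True = 0.10 + 0.90/11.7 = 0.177; model = 1.00/11.7 = 0.086. SE ratio = √(0.086/0.177) = 0.70; error 17%.

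| ICC | CAC | Model SE/true SE | Actual error |
|---|---|---|---|
| 0.10 | 0.5 | 0.70 | 17% |
| 0.10 | 0.8 | 0.83 | 10% |
| 0.10 | 0.95 | 0.95 | 6.4% |
| 0.05 | 0.9 | 0.95 | 6.3% |
| 0.02 | 0.8 | 0.96 | 6.0% |
| any | 1 | 1.00 | 5.0% |

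These rows give both arms the same brothel-by-time variance. If only the experimental brothels varied (CAC 0.5 there, CAC 1 in control, ICC 0.10), the average true variance is (0.177 + 0.077)/2 = 0.127 and the pooled model variance is 0.95/11.7 = 0.081. The SE ratio is 0.80 and the error about 12%.

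**The same result by the within-brothel correlation of change**, ρ = a/(a + b). True SE/model SE = √[1 + (m − 1)ρ], with coverage of a nominal 95% interval in brackets:

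| ρ | m = 16.7 (no loss) | m = 11.7 (30% lost) | m = 8.3 (50% lost) |
|---|---|---|---|
| 0 | 1.00 (95.0%) | 1.00 (95.0%) | 1.00 (95.0%) |
| 0.01 | 1.08 (93.2%) | 1.05 (93.8%) | 1.04 (94.1%) |
| 0.05 | 1.34 (85.8%) | 1.24 (88.7%) | 1.17 (90.6%) |
| 0.10 | 1.60 (77.9%) | 1.44 (82.7%) | 1.32 (86.3%) |

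**Simulation of the three-level logistic model.** Random intercepts for women and brothels only, fitted by quadrature; 12 brothels of 5 to 38 women (200 in all), 30% lost, no true effect, 1000 trials per row. Assumed logit-scale variances: women 1.5, stable brothel effect 0.4, brothel-by-time as shown (per occasion). The implied CAC is 0.4/(0.4 + brothel-by-time variance).

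| Brothel-by-time variance | Implied CAC | True SE/model SE | Coverage, z | Coverage, t(10) |
|---|---|---|---|---|
| 0 | 1 | 1.00 | 95.8% | 97.9% |
| 0.05 | 0.89 | 1.04 | 94.3% | 97.6% |
| 0.15 | 0.73 | 1.19 | 90.4% | 93.5% |
| 0.30 | 0.57 | 1.37 | 85.2% | 90.6% |

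The Monte Carlo standard error is about 0.7 points at 95% and 1.1 points at 85%. Swapping z for t(10) without the missing component is no repair: it over-covers in the first row and under-covers in the last.

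**Small number of brothels.** Once between-brothel change is modelled, the reference is about t on 12 − 2 = 10 df. The critical value is 2.228 against 1.960, 13.7% wider. Using z where t(10) applies gives 7.8% error. In a separate simulation of a random-intercept logistic model on follow-up data alone (close to the alternative fix, not the planned model), z gave 7.9%, 8.7% and 10.1% at latent ICC 0.06, 0.10 and 0.20; t(10) gave 5.1% to 5.9%.

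**The ICC.** In the linear case, a time-constant brothel intercept returns ICC·(1 + CAC)/2. With a 16-week ICC of 0.10 this is 0.10 × 1.5/2 = 0.075 at CAC 0.5 and 0.10 × 1.8/2 = 0.09 at CAC 0.8, both below 0.10.

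**The case against.** The strongest reply is that the article never restricts brothel to an intercept. A three-level model can carry a random time effect for brothels, and an article often leaves the random-effect structure, the form of the contrast and the reference distribution to a fuller plan. It also does not say which ICC it will report. What it does state, that brothels are randomized and are in the model, is right. This stands in part: intercept-only is the natural reading of the listed levels, not a quotation. But the article does fix baseline and follow-up as level-1 outcomes and offers the levels as its answer to clustering. For an arm-by-time effect, the listed levels alone do not provide that answer.

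Second, the brothel-by-time variance could be small, and no figure for it is given. This also stands. With none, coverage was nominal.

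Third, the analysis is secondary. The measurements section makes feasibility, attrition and adherence primary, and the discussion makes the next trial conditional on feasibility, not on a significant effect. That limits the consequence, but the effect size and ICC remain planned inputs to phase III.

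Fourth, a brothel-by-time variance is hard to estimate from 12 brothels, some with about five women, with separate models by partner type. This is true, and it bears on the choice of fix.

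**Conclusion.** The point holds as a conditional one. If the listed levels are fitted as random intercepts, and brothels differ in how much they change, the standard error of an arm-by-time effect is understated. At about 12 completers per brothel, the nominal 5% error runs from 5% with no brothel-by-time variance to about 17% at ICC 0.10 and CAC 0.5. Simulated coverage of the three-level logistic model ran from about 95% to 85%. Every ICC, autocorrelation and attrition figure behind these is an assumption.

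A reader might infer three stronger things, and the article supports none of them:

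- That the intervals will certainly be too narrow, or that the error is at least 10%. With high brothel autocorrelation or a low ICC it is 5% to 6.4%.
- That having 12 brothels makes the planned analysis anti-conservative by itself. With no brothel-by-time variance, normal-based intervals from 12 brothels covered 95.8%. The z-versus-t problem arises once between-brothel change is in the model.
- That the pilot's main conclusions are at risk. The primary feasibility outcomes do not depend on this model.

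**What to change.** State in the analysis section one of two models, which are alternatives and not equivalents:

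1. the three-level model with a brothel-by-time random effect added; or
2. the 16-week outcome with the baseline value as covariate and a brothel random effect.

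With either, base intervals on a small-sample reference (t on about 10 df, assuming six brothels per arm), and give a brothel-level analysis as a check. Report the ICC of the 16-week outcome, so that phase III is planned on the quantity it needs.

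The change is to analysis wording only. No recruitment, allocation or data collection changes, and the article describes the pilot as still underway. The costs are wider intervals and, under option 1, a brothel-by-time variance imprecisely estimated from 12 brothels. That favours option 2 or the brothel-level version.
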